# Extracorporeal carbon dioxide removal for acute hypercapnic exacerbations of chronic obstructive pulmonary disease: study protocol for a randomised controlled trial

**DOI:** 10.1186/s13063-019-3548-4

**Published:** 2019-07-30

**Keywords:** Acute exacerbations of chronic obstructive pulmonary disease, COPD, Extracorporeal CO_2_ removal, ECCO2R, Non-invasive ventilation, NIV

## Abstract

**Background:**

Chronic obstructive pulmonary disease (COPD) is a common cause of chronic respiratory failure and its course is punctuated by a series of acute exacerbations which commonly lead to hospital admission. Exacerbations are managed through the application of non-invasive ventilation and, when this fails, tracheal intubation and mechanical ventilation. The need for mechanical ventilation significantly increases the risk of death. An alternative therapy, extracorporeal carbon dioxide removal (ECCO_2_R), has been shown to be efficacious in removing carbon dioxide from the blood; however, its impact on respiratory physiology and patient outcomes has not been explored.

**Methods/design:**

A randomised controlled open label trial of patients (12 in each arm) with acute exacerbations of COPD at risk of failing conventional therapy (NIV) randomised to either remaining on NIV or having ECCO_2_R added to NIV with a primary endpoint of time to cessation of NIV. The change in respiratory physiology following the application of ECCO_2_R and/or NIV will be measured using electrical impedance tomography, oesophageal pressure and parasternal electromyography. Additional outcomes, including patient tolerance, outcomes, need for readmission, changes in blood gases and biochemistry and procedural complications, will be measured. Physiological changes will be compared within one patient over time and between the two groups. Healthcare costs in the UK system will also be compared between the two groups.

**Discussion:**

COPD is a common disease and exacerbations are a leading cause of hospital admission in the UK and worldwide, with a sizeable mortality. The management of patients with COPD consumes significant hospital and financial resources. This study seeks to understand the feasibility of a novel approach to the management of patients with acute exacerbations of COPD as well as to understand the underlying physiological changes to explain why the approach does or does not assist this patient cohort. Detailed respiratory physiology has not been previously undertaken using this technique and there are no other randomised controlled trials currently in the literature.

**Trial registration:**

ClinicalTrials.gov, NCT02086084.

**Electronic supplementary material:**

The online version of this article (10.1186/s13063-019-3548-4) contains supplementary material, which is available to authorized users.

## Background

Chronic obstructive pulmonary disease (COPD) is a syndrome characterised by progressive and not fully reversible expiratory airway flow limitation. The underlying pathophysiology of COPD is the progressive destruction of the elastic and alveolar tissue within the lung, resulting in reduced expiratory flow rates, maldistributed ventilation, gas trapping and hyperinflation, which in turn lead to diaphragmatic flattening and inefficient respiration. COPD is punctuated by recurrent exacerbations characterised by a worsening of the patient’s dyspnoea, cough and/or sputum production beyond day-to-day variations [1]. Acute exacerbations are an important cause of hospital admission and impact on patients’ quality of life [2–5], as well as having a huge societal impact amounting to ~ 6% of the total healthcare cost [6]. Exacerbations also accelerate disease progression, leading to a progressive stepwise functional decline [7–13].

Patients with significant exacerbations of COPD resulting in hypercapnic respiratory acidosis (PaCO_2_ > 6 kPa (45 mmHg) and pH < 7.35) have life-threatening respiratory failure and non-invasive ventilation (NIV) has significant mortality benefits for patients [1, 14–19]. NIV provides both inspiratory and expiratory pressure, which, by splinting open collapsing airways by matching intrinsic positive end expiratory pressure (PEEP) and providing positive pressure to assist tiring respiratory muscles, enhances ventilation. This enables an improved ventilation–perfusion relationship, improves gas exchange and simultaneously reduces oxygen consumption and carbon dioxide production because of the reduction in work of the respiratory muscles [16, 20]. Although NIV has substantially improved mortality (risk ratio 0.54, 95% CI 0.38 to 0.76) and decreased the need for intubation (risk ratio 0.36; 95% CI 0.28 to 0.46) in patients with an acute exacerbation of COPD [16], 15–30% of patients commencing NIV fail and require intubation and mechanical ventilation [21–23]. Risk factors for NIV failure include obtundation, hypercapnoea, persisting respiratory acidosis (pH < 7.30), higher APACHE II score (> 28), tachypnoea (> 29) and lack of improvement in the first 1–2 h of therapy [23–27]. Patients who fail NIV and require intubation have a significantly higher mortality than those who improve with NIV (30% vs < 10%) [28], with mortality rates up to 57% in some case series [29].

Extracorporeal CO_2_ removal (ECCO_2_R) is the use of an extracorporeal circuit with a gas-exchanging membrane to provide clearance of CO_2_ directly from the blood [30, 31]. ECCO_2_R has been reported to clear CO_2_ in the pre-clinical setting [32–37] as well as in uncontrolled case series which have included patients with acute exacerbation of COPD (AECOPD) [35, 38–42]. Potential benefits, including avoidance of intubation and early extubation, have been suggested from this retrospective work; however, a retrospective propensity matched case-control study using ECCO_2_R in COPD reported no significant improvement in mortality [43].

In addition to an unclear mortality benefit, it is also uncertain what the impact of ECCO_2_R is on native lung physiology. There is a widely reported reduction in respiratory rate and minute ventilation with improvements in pH and partial pressure of arterial CO_2_ [33, 39, 41, 42, 44, 45]. A small pilot study reported on the changes associated with ECCO_2_R in patients with COPD weaning from a ventilator and found that intrinsic PEEP, inspiratory pulmonary resistance and work of breathing were all reduced [46]. The authors postulated that part of the reduction in arterial CO_2_ seen in these patients was due to both the direct effects of CO_2_ removal and the reduced respiratory muscle work.

Despite ECCO_2_R showing promise as a method to reduce respiratory work and avoid intubation in uncontrolled case series and a propensity analysis, there have been no randomised controlled trials of ECCO_2_R in AECOPD and limited data are available on the physiological impact of ECCO_2_R on respiratory function and work of breathing in AECOPD. Hence, the key clinical role and physiological effect of ECCO_2_R needs greater definition and this work is aimed to explore both the outcome for patients with AECOPD commenced on ECCO_2_R and to better understand the physiological effects of ECCO_2_R in COPD exacerbations.

## Trial hypothesis and objectives

The main hypotheses for the trial are that ECCO_2_R will lead to a significant reduction in the need for NIV and that this is mediated through a reduction in work of breathing secondary to the reduced CO_2_ burden. To explore work of breathing, several methods of assessing work of breathing will be undertaken: oesopheageal pressure monitoring, electrical impedance tomography and parasternal electromyography. These methods have not been used in combination before in this population; however, the benefit of using multimodal monitoring in the setting of acute exacerbations of COPD is that it will allow correlation between the different measurements and it is possible that one or more methods may not be able to be used in an individual patient.

## Methods/design

### Design

The trial is a prospective, randomised, controlled, with 1:1 allocation ratio unblinded study of ECCO_2_R in adults with AECOPD at risk of failing NIV as demonstrated by a persisting pH < 7.30 due to hypercapnoea after initial medical therapy and at least 1 h of NIV. The study will randomise a total of 24 patients, 12 in each treatment arm. Allocation was generated by computer-generated random number and concealed via opaque sealed envelopes.

### Inclusion criteria

Known COPD with an acute exacerbation. An acute exacerbation is defined as per the GOLD criteria as an increase in dyspnoea, cough and/or sputum over the patient’s normal symptoms. A severe exacerbation is defined as one requiring hospital admission. Patients are known to have COPD when they have a previous diagnosis made and recorded on their medical records, data in support of this will include chest imaging, pulmonary function tests and clinical history/examination.Patients with a persistent arterial pH < 7.30 due primarily to hypercapnic respiratory failure after standard medical therapy and at least 1 h of NIV.Age over 18

### Exclusion criteria

Haemodynamic instability after ensuring euvolaemiaMultiple organ failure requiring other organ supportive therapy, including indication for intubation and mechanical ventilation; this includes requirement for chronic organ supportive therapy (e.g. chronic non-invasive ventilation, dialysis)Known allergy/intolerance of heparin including known heparin-induced thrombosis and thrombocytopaeniaAcute uncontrolled haemorrhageIntracerebral haemorrhageRecent (< 6 months) ischaemic cerebrovascular accidentOrgan transplant recipientExpected to die within 24 h or with limitations of therapy in place precluding admission to critical careVenous abnormality or body habitus precluding cannulationContraindication to NIV (as per British Thoracic Society recommendations):Facial burns/trauma/recent facial or upper airway surgeryVomitingFixed upper airway obstructionUndrained pneumothoraxRecent upper gastrointestinal surgeryInability to protect the airwayLife-threatening hypoxaemia (PaO_2_/FiO_2_ < 20 kPa)Bowel obstructionPatient refusalPregnancySevere hepatic failure (ascites, hepatic encephalopathy or bilirubin > 100 μmol/L)Severe chronic cardiac failure (NYHA class III or IV)Bleeding diathesis (INR > 1.5, platelets < 80,000) in the absence of anticoagulation therapy

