### Secondary outcome

Secondary outcomes include the impact of ECCO2R on:Safety, including:Incidence of haemorrhagic complications—significant haemorrhage is defined as bleeding requiring transfusion of more than one unit of blood, intracerebral bleeding, bleeding requiring procedural interventionIncidence of thrombosis—all patients will have screening duplex ultrasound of the cannulated vesselIncidence of haemolysis defined by rising lactate dehydrogenase, bilirubin red cell fragments on a blood film and/or a rising plasma free-haemoglobin (> 0.5 g/dL)Complications relating to cannulation including those at insertion—bleeding, vascular damage, pneumothorax and line infection, both clinically apparent (erythema/cellulitis at insertion site) and microbiologically proven (positive blood culture with concomitant line tip culture or line insertion site culture)Physiology, including respiratory rate, heart rate, blood pressure, temperature, arterial blood gases measured at time (T)0 min, T30 minutes, T 60 min, then every fourth hour for the first 24 h and then every sixth hour until discontinuation of the acute phase of the trialDaily spirometry including forced vital capacity, forced expiratory volume in 1 s and the ratio between themWork of breathing, including electrical impedance tomography, parasternal electromyography and oesophageal pressure (these are described in detail below)Patient outcomes:Mortality (ICU, hospital and 3 month)Length of stay (ICU, hospital)Need for intubation and where this occurs, duration of mechanical ventilation and need for tracheostomy, NIV failure and need for intubation will be decided by the clinical team managing the patient. Reason for NIV failure will be recorded by the research team.3-Month hospital readmission rateTolerance, assessed using both a numerical rating scale (0–10) and visual acuity scale (0–10 cm) for both dyspnoea and comfort with the lowest reading being extremely uncomfortable and the highest being extremely comfortable. Comparisons between the two different measures will be used without an absolute definition of comfort/discomfort.At 3-months following randomisation: COPD assessment test, St George’s Respiratory Questionnaire, EuroQoL 5D. Comparisons between the different measures will be used without an absolute definition of success at follow-up.Cost-effectiveness with ICU bed day and consumables cost/quality adjusted life year (QALY)

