### Treatment of trial participants

Following presentation, initial medical therapy and NIV will be commenced as per current local and UK national guidelines for the management of AECOPD [47]. All patients with AECOPD and pH < 7.30 after a minimum of 1 h NIV will be eligible for inclusion unless exclusion criteria are met. Once informed written consent is obtained from either the patient or their consultee if consent from the patient is not possible, patients will be randomised to the continuation of NIV alone or addition of ECCO_2_R to NIV. All other aspects of care, including acute, on-going and post-trial care, will be at the discretion of the clinical team. Monitoring will be the standard of care of ICU, including arterial and central venous access where this is deemed appropriate by the clinical team.

Patients who are randomised to continuation of NIV alone will be managed in accordance with hospital protocols and national guidelines for NIV. NIV will be titrated to achieve an arterial pH > 7.35, respiratory rate < 25 and patient comfort with breathing. Discontinuation of NIV will occur when judged appropriate by the patient’s clinician. Cessation of NIV will be defined as occurring after six continuous hours without NIV.

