#### ECCO_2_R

Patients who are randomised to addition of ECCO_2_R will undergo cannulation in either the right internal jugular vein or one of the femoral veins using a 15.5 French double lumen ECCO_2_R cannula (patient and operator preference) using an ultrasound-guided Seldinger technique. The ECCO_2_R device, will be primed with 0.9% saline and 1 unit/mL heparin in accordance with the manufacturer’s instructions. The blood flow will be titrated to the maximum achievable (usually 400–500 mL/minute) and sweep gas titrated up to 10 L/minute in 1 L/minute increments every 15 min. ECCO_2_R will be titrated to achieve an arterial pH > 7.35, respiratory rate < 25 and patient comfort with breathing. Discontinuation of NIV and ECCO_2_R will occur when judged appropriate by the patient’s clinician. Cessation of ECCO_2_R will be defined as occurring after six continuous hours without ECCO_2_R. All patients receiving ECCO2R will receive a continuous infusion of heparin to maintain an APTTr of 1.5–2 titrated using the hospital protocol. Data relating to the ICU inpatient stay will be collected from the ICU and hospital information systems. At 3 months following randomisation, a telephone interview will be conducted by the randomising study centre to ascertain the post-discharge survey data.

Whilst the patient remains on respiratory support (either NIV or ECCO_2_R), all patients will undergo daily assessment of dyspnoea and comfort, spirometry, electrical impedance tomography, parasternal electromyography and oesophageal pressure monitoring.

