## Sites and site monitoring

The study will be conducted at up to five sites within the UK and monitored according to the standard operating procedure for site monitoring of the GSTT Trials Unit, which includes at least one site visit over the course of the trial as well as triggered visits if required. All data from the sites will be shared solely with the co-ordinating centre. Local sites will liaise directly with the manufacturers for equipment/disposables. The lead site will supervise all other aspects of the study and is available 24 h, 7 days for questions relating to the study. The randomisation sequence is solely held at the lead centre who will also allocate trial participant numbers. All sites are University-affiliated hospitals with tertiary intensive care units experienced in the provision of extracorporeal CO_2_ removal. Current sites include Guy’s and St Thomas’ NHS Foundation Trust, Manchester University NHS Foundation Trust, Chelsea and Westminster NHS Foundation Trust and Queen Elizabeth University Hospital, Glasgow. Additional data about sites can be obtained from the corresponding author. Source data verification conducted over the course of the trial will be at least 1% and will increase if significant discrepancies are found.

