## Protocol amendments

Protocol amendments will be approved by both the sponsor and the REC prior to being implemented. Any protocol amendments will be numbered and dated and shared with investigating centres to ensure version control.

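### Read literally, the bleeding exclusion waives its platelet limit as well as its INR limit for anticoagulated patients

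*Protocol article*

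**What the plan says.** The protocol article lists as an exclusion (Exclusion criteria): "Bleeding diathesis (INR > 1.5, platelets < 80,000) in the absence of anticoagulation therapy". The section Treatment of trial participants makes exclusion the only bar for patients who meet the COPD, pH and NIV conditions: they "will be eligible for inclusion unless exclusion criteria are met".

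Under ECCO2R, patients allocated to the device are cannulated in a jugular or femoral vein with a "15.5 French double lumen" cannula, and "All patients receiving ECCO2R will receive a continuous infusion of heparin to maintain an APTTr of 1.5–2 titrated using the hospital protocol".

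Bleeding is also an outcome. Under Secondary outcome, "significant haemorrhage is defined as bleeding requiring transfusion of more than one unit of blood", with intracerebral bleeding and bleeding that needs a procedure also counting.

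**The concern.** An anticoagulant ordinarily explains a raised INR. It does not ordinarily explain a low platelet count. That is general clinical knowledge and is not stated in the article. The main exception is heparin-induced thrombocytopenia, which the article excludes separately when it is known.

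It therefore makes sense to excuse a raised INR in a patient on an anticoagulant, but there is no evident reason to excuse a low platelet count on the same ground. As printed, the qualifier can be read to excuse both. A patient with a count of 70,000 (in the criterion's own unit) and no anticoagulant would be excluded, while a patient with the same count who takes an anticoagulant would be admitted. That ordering runs against bleeding risk.

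What is at stake is patient safety at entry. The authors judged a platelet limit necessary, and the wording can switch it off for one group.

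**Working it through.** No calculation applies, because the point concerns the wording of an eligibility rule. The check has three steps.

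**Step 1: apply each reading of the qualifier.** The literal reading attaches it to everything in the bracket. The causal reading excuses only an abnormality that the anticoagulant explains. The INR-only reading attaches it to the INR limit alone.

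| Patient | Literal | Causal | INR-only |
|---|---|---|---|
| No anticoagulant, INR above 1.5 | excluded | excluded | excluded |
| No anticoagulant, platelets below 80,000 | excluded | excluded | excluded |
| On anticoagulant, INR above 1.5 because of it | not excluded | not excluded | not excluded |
| On anticoagulant, platelets below 80,000 from another cause | **not excluded** | excluded | excluded |

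Among these four cases the readings differ only in the last row. The table takes either limit as sufficient to exclude. The article separates the two limits with a comma and does not say whether one or both must be met, which is a second, smaller ambiguity in the same item.

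**Step 2: look for another item that would catch the last row.** The nearest exclusions are:
- heparin allergy or intolerance, which covers low platelets only when they are known to be heparin-induced;
- uncontrolled bleeding and bleeding in the brain, which need an actual bleed;
- severe liver failure, defined by ascites, encephalopathy or bilirubin;
- haemodynamic instability, and multiple organ failure needing support.

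Each may remove some patients with low platelets. None sets a platelet limit, and none covers low platelets from other causes in an otherwise eligible patient on an anticoagulant. By the eligibility rule in Treatment of trial participants, that patient may then enter under the literal reading.

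**Step 3: see what follows entry.** If allocated to ECCO2R, the patient receives the cannula and the heparin infusion. The ECCO2R section gives no platelet condition for starting either.

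The literal reading therefore opens a gap that the rest of the article does not close. The other two readings leave no gap, but the text does not choose between the three.

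**The case against.** **The intended meaning is plain to a clinician.** The subject of the item is a bleeding diathesis, and an intensivist would naturally take the qualifier to mean one not explained by anticoagulants. This largely stands: the causal reading is probably what was intended. It does not remove the point, because an entry limit should give every reader the same answer.

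**The article condenses a fuller protocol.** The version held by sites is not shown and may already separate the limits. This also stands as a caveat. However, the article prints the criterion with both cut-offs, so the issue is how a stated rule is worded and not a detail left out.

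**Central allocation protects against inconsistent reading.** Under Randomisation and codebreaking, other sites telephone the lead centre and only the primary study team opens envelopes. Under Sites and site monitoring, the lead site can be asked about the study at any hour, and all sites have ECCO2R experience. This substantially lowers the chance that such a patient is enrolled. It relies on someone noticing and overriding the wording.

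**Stronger inferences that the documents do not support.**
- A reader might infer that the trial means to admit anticoagulated patients with low platelets, or has done so. Nothing in the article shows either.
- A reader might try to size the harm from the design: "The study will randomise a total of 24 patients, 12 in each treatment arm". The chance of being allocated to ECCO2R, or the share of an arm that one bleed represents, follows from the allocation ratio and arm size for any patient and any bleed. Neither measures bleeding risk added by this wording, and the documents give no figure for that risk or for how often such patients present.
- A reader might infer a threat to the efficacy result. The criterion does not enter the primary outcome, the sample size or the analysis.

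**Conclusion.** The point holds as a minor wording fault with a bearing on patient safety. As written, the qualifier follows a bracket containing both limits, so its literal reading waives the platelet limit for anticoagulated patients, and no other item in the article restores it.

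No magnitude is claimed. For harm to occur, a patient would need low platelets, concurrent anticoagulation and none of the other exclusions; the literal reading would have to be applied and pass the lead centre; and the patient would have to be allocated to ECCO2R. That sequence is probably very rare in a trial of 24.

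The conclusion rests on two assumptions: that the wording used at sites matches the article, and that anticoagulants do not ordinarily cause a low platelet count. If the sites' version already separates the limits, only the published wording is at fault.

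**What to change.** Split the item into two exclusions:
- *platelets < 80,000, regardless of anticoagulation*;
- *INR > 1.5, unless explained by anticoagulant therapy*.

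Listing them separately also makes clear that either one excludes. No new test is needed, since the existing item already calls for INR, platelet count and anticoagulant status at screening.

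First check the protocol version held by sites. If it already separates the limits, no change is needed there. If not, the trial was still recruiting when the article was submitted, so a change could still protect later patients. As an amendment it falls under the stated rule: "Protocol amendments will be approved by both the sponsor and the REC prior to being implemented". It must also be numbered, dated and shared with the investigating centres ("The study will be conducted at up to five sites within the UK"). Whether a clarification note would be enough is for the sponsor to decide.

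The only other cost is possibly a very few lost candidates. Later recruits would replace them, so the target stays at 24 and the price is some recruitment time.
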